### Data collection

All efficacy parameters will be collected during hospitalization of the patient in the ICU. In case of hospital discharge, phone calls will be made by the investigators or the research team with at least three attempts to contact the patient, his/her physician, or the patient’s emergency contact in a period of 10 days at different times of the day. If there is no answer, vital statistics will be collected via contact of the town council of the patient’s birthplace.

Data will be collected by the investigators and their teams in an electronic case report form (e-CRF). Data will be monitored by a clinical research associate (CRA) and checked for consistency and missing values by a data manager.

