### Statistical analysis

The study is designed to demonstrate the non-inferiority on the composite endpoint of mortality and recurrence at 90 days of the 8-day strategy versus the 15-day strategy for PA-VAP. Considering the mortality and/or recurrence of PA-VAP rate of 35.7% [7], 284 patients will be required in each group to achieve a power of 80% to exclude a 10% difference between the two groups with an α risk of 5%. To account for a possible 5% patient loss to follow-up, we planned to enroll 600 patients.

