### Data analysis

Baseline characteristics of patients will be described per group. Qualitative data will be described with frequencies and percentages; quantitative data will be described with mean and standard error or with median, interquartile interval, and range. Since this is a non-inferiority study, analysis of principal criteria will be performed on a per protocol population. The per protocol population will be defined as randomized patients without major protocol deviations such as non-respect of all selection criteria, clear non-respect of the antibiotic duration allocated (+/– 24 hours), missing data for the primary endpoint, and major protocol deviation(s) identified during a blinded data review before data base freezing. Non-inferiority will be tested by a Dunnett and Gent chi-squared procedure [21]. Secondary analysis in an intent-to-treat (ITT) population will also be performed.

Secondary outcomes will be analyzed under a superiority assumption. Day 30 and day 90 mortality rates and acquisition of MDR pathogens during hospitalization in the ICU will also be compared between groups by a chi-squared test or a Fisher’s exact test, if the use conditions were not verified. Duration of mechanical ventilation, duration of hospitalization in the ICU, duration of exposure to antibiotics, and number of extrapulmonary infections during hospitalization in the ICU will be compared between groups by Student *t* tests or Mann-Whitney/Wilcoxon tests, if needed. Types of extrapulmonary infections will be described.

The association between respiratory colonization with yeast at diagnosis and PA recurrence will be studied by logistic regression adjusted on the randomization group. The association between monotherapy or combination therapy and mortality and PA recurrence will be studied by a logistic regression adjusted on the randomization group. Procalcitonin levels at days 0, 1, 3, and 7 will be described, and their prognosis values on mortality and *P. aeruginosa* recurrence will be studied by logistic regression and sensitivity and specificity analyses. Missing data will be not replaced.

The study will be conducted in accordance with the Helsinki Declaration and French laws and regulations. The study has received its approval from the French ethics committee (Comité de Protection des Personnes Ile de France VI) as well from the French Drug Safety Agency (Agence Nationale de Sécurité du Médicament et des Produits de Santé) (EudraCT 2015-003102-17).

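### Patients with a missing primary endpoint drop out of both the per-protocol and, as written, the ITT analysis, so agreement between the two does not test loss to follow-up

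*Protocol article*

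**What the plan says.** Under Data analysis, the article states that "analysis of principal criteria will be performed on a per protocol population". Its list of major deviations that remove a patient from that population ends with "missing data for the primary endpoint, and major protocol deviation(s) identified during a blinded data review before data base freezing". It then says "Secondary analysis in an intent-to-treat (ITT) population will also be performed", without defining how that analysis treats an unknown endpoint. The section's only rule on missing values is "Missing data will be not replaced"; it names no exception for the primary endpoint or for the ITT set.

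Under Statistical analysis, loss is met by recruitment: "To account for a possible 5% patient loss to follow-up, we planned to enroll 600 patients".

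Two other sections limit the problem. Assessment criteria counts recurrence only during the ICU stay, within 90 days, and makes the endpoint recurrence and/or death. Data collection provides for at least three contact attempts after discharge, and if these fail, "vital statistics will be collected via contact of the town council of the patient’s birthplace".

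**The concern.** In a non-inferiority trial with a per-protocol primary analysis, the ITT analysis is the check on what the exclusions did. For duration and eligibility deviators it can do that, because they return to the comparison. For patients with an unknown endpoint it cannot: they are excluded from per protocol by definition and, if nothing is substituted, have no outcome to contribute to ITT. The check repeats the exclusion it should test.

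If loss were related to outcome and differed between arms, both analyses would shift together, and their agreement could be taken for robustness. Enrolling more patients restores precision but does nothing about such a shift. This is a rule that the article states, not a detail that it leaves open.

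**Working it through.** **Inputs.** Event rate 35.7%, 284 per group, 80% power, 10-point margin, α of 5%, 5% loss and 600 enrolled (Statistical analysis); 1:1 allocation (Randomization). An even split of the loss, and the outcomes of lost patients, are assumptions; the document gives neither.

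**The plan's own figure.** With the same rate in both arms and one-sided α of 5%:

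n = 2 × 0.357 × 0.643 × (1.645 + 0.842)² / 0.10² = 283.8, so 284 per group.

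The total of 568 / 0.95 = 597.9, or 598, is rounded to 600. The stated figures reproduce. At one-sided 2.5% the formula gives 361, so a one-sided 95% upper limit matches the design.

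**Who is analysed.**

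| Patient | Per protocol | ITT, as written |
|---|---|---|
| Wrong duration or ineligible, endpoint known | out | in |
| Endpoint unknown | out | no value, none substituted |

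The two sets differ in the first row and coincide in the second.

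**A bound on what is hidden.** Upper limit = d + 1.645 × √[p₁(1−p₁)/n₁ + p₀(1−p₀)/n₀], with d = p₁ − p₀, where 1 is the 8-day arm and 0 the 15-day arm.

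*5% loss:* 300 randomised and 15 lost per arm, leaving 285 with 102 events (0.357 × 285 = 101.7).
- Lost patients omitted: d = 0, standard error 4.02 points, upper limit 6.6.
- All lost counted as events in both arms: 117/300 in each, d = 0, upper limit 6.6.
- Extreme allocation (every lost 8-day patient an event, no lost 15-day patient one): 117/300 = 39.0% against 102/300 = 34.0%; d = 5.0, standard error 3.93, upper limit 11.5.

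*1% loss:* 3 lost per arm, 106/297 observed in each. Extreme allocation: 109/300 against 106/300; d = 1.0, standard error 3.92, upper limit 7.4.

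**Where it tips at 5% loss.** With no events among the 15 lost 15-day patients:
- 10 events among the lost 8-day patients: 112/300 against 102/300, d = 3.33, upper limit 9.8.
- 11 events: 113/300 against 102/300, d = 3.67, upper limit 10.1.

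With equal observed rates, crossing the margin therefore needs at least 11 of 15 lost patients to be events in one arm and none of 15 in the other. If the observed result were already less favourable, 108/285 against 102/285 (d = 2.1, upper limit 8.8), five events among the lost 8-day patients and none among the lost 15-day patients would give the same 113/300 against 102/300, and 10.1.

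**The case against.** The strongest objection is that few endpoints will be missing. Recurrence is settled before ICU discharge, and a register that identifies deaths normally also identifies those not recorded as dead. A discharged survivor who does not answer the telephone is then a known non-event. True missingness is confined to patients for whom telephone and register both fail. The 5% is called only possible and serves as a recruitment allowance. This stands, and it is why the effect is probably small.

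Second, the no-replacement sentence closes a paragraph on exploratory regressions and procalcitonin, so its scope could be narrower. That is arguable, but the wording is general and no other missing-data rule appears.

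Third, methods for missing data usually belong in an analysis plan, which is not shown. That holds for the choice of imputation method, which is not part of this point. It does not hold for a stated rule that a later plan would be expected to follow.

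A reader might infer that the loss will bias the comparison by several points. The documents do not support that. If untraced patients are mostly event-free and loss is equal, 5% loss raises both rates to 0.357/0.95 = 37.6% and leaves the difference at zero. Unequal loss of 2% against 8% would give 36.4% against 38.8%, a gap of 2.4 points, but that split is assumed and the same tracing applies to both arms. The extreme allocation behind 11.5 points assumes the opposite: that every lost 8-day patient had an event.

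**Conclusion.** The point holds in a limited form. As the rules are written, patients with an unknown primary endpoint are missing from both analyses, and agreement between them is no evidence about loss to follow-up. It remains evidence about duration and eligibility deviations, so a reader who concluded that the ITT analysis is worthless as a check would go too far.

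The likely effect is small. The range from 7.4 points (about 1% loss) to 11.5 points (5% loss) for the upper limit is a bound under extreme allocation, not an expected bias. It rests on equal observed rates near 35.7%, even loss between arms and a simple unpooled normal interval. What can be said firmly is that, at the loss the plan allows for, the stated analyses could not show whether a non-inferiority conclusion survives. This is a worthwhile, cheap improvement; the sample size need not change.

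**What to change.** For the primary endpoint, replace the no-replacement rule with the following, settled before the database is frozen:

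1. The ITT analysis includes all randomised patients in the arm assigned.
2. An adjudicated recurrence or a known death within 90 days counts as an event whatever the later follow-up. The and/or definition implies this; saying so prevents such patients from being classed as missing.
3. For patients whose day-90 status is still unknown after tracing, a pre-specified tipping-point sensitivity analysis varies the assumed events from all in the 8-day arm and none in the 15-day arm to the reverse, and reports whether the upper confidence limit stays below 10 points.
4. The number with a missing endpoint is reported by arm.

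Multiple imputation within arm could be added but is optional. The cost is a few lines of text and a little programming, with no change to data collection; the downside is a possibly less favourable limit. If tracing works as described, the analysis will show that few patients are missing and that the conclusion does not depend on them.

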## Discussion

This study will investigate the influence of duration of antibiotic therapy on mortality and recurrence of PA-VAP. Our goal is to demonstrate that a short antibiotic therapy (8 days of effective antibiotic therapy) compared to a long antibiotic therapy (15 days of effective antibiotic therapy) is safe without excess mortality or recurrence, and decreases the duration of exposure to antibiotics and the acquisition of MDR pathogens. Furthermore, this study will evaluate the relationship between PA recurrence and (1) respiratory colonization with yeast at diagnosis, (2) treatment with monotherapy or combination therapy, and (3) procalcitonin levels during the course of VAP.

We believe that the present study has several strengths. First, it specifically addresses the issue of recurrence of PA-VAP, and the number of patients to be included (*n* = 600) has been calculated according to an expected rate of 35% for the composite endpoint combining 90 day mortality and PA-VAP recurrence as shown in a previous study [7]. This expected rate is in accordance with previously published data. Hence, Combes et al. reported a recurrence rate of 28% [22]. In a meta-analysis, the frequency of VAP recurrence was 26.8%. Acute lung injury/acute respiratory distress syndrome and shock on the day of diagnosis of the first VAP episode, but not the first-episode causative pathogens, were found to be associated with VAP recurrence [23]. Finally, in the cohort published by Planquette et al. on 314 patients with 393 PA-VAP, failure occurred for 112 of them (35.7%), including 79 recurrences (20.1%) [7].

Crouch Brewer et al. reported in a cohort of 38 consecutive PA-VAP a mortality of 69% with an attributable mortality of 38% [4]. We can emphasize that persistent pneumonia occurred in 35% of patients while recurrence of pneumonia was unusual (1/38). Trouillet at al. reported a cohort of 135 PA-VAP. In this cohort, 70 patients (52%) died during the ICU stay, and only 10 patients had recurrences [5]. Finally, in a retrospective, multicenter, observational cohort study conducted in five Spanish ICUs, Garnacho-Montero et al. reported 183 monomicrobial episodes of PA-VAP, with a mortality of 42.1% [6], and an Italian retrospective analysis of data prospectively collected about 110 cases of PA-VAP and reported an ICU mortality of 44.5% [24].

The study is open-labeled, because a double-blind study would have presented considerable financial and organizational constraints. Thus, we cannot completely rule out the risk of bias, especially the non-compliance with the antibiotic therapy duration. Nevertheless, first, investigators received clear instructions about the crucial importance of compliance with the treatment allocation. Second, the comparison of the duration of exposure to antibiotics between groups and between centers will give us an indication about non-compliance with study arms. Third, post hoc analysis of the primary endpoint will be conducted without any knowledge of the study arm.

In conclusion, this study should contribute to determine the most appropriate duration of antibiotic therapy treatment in the specific case of PA-VAP to decrease both mortality and the recurrence rate of PA-VAP. If our hypothesis is confirmed, the study may lead to decreased antibiotic exposure during the hospitalization in ICU and in turn reduce the acquisition and the spread of MDR. The therapeutic perspectives which could result from this study are thus promising.

### Trial status

The first patients were randomized in June 2016. The inclusion of participants is ongoing and is expected to continue until June 2018.

## Abbreviations

COPD: Chronic obstructive pulmonary disease
ICU: Intensive care unit
MDR: Multidrug-resistant (pathogens)
PA: *Pseudomonas aeruginosa*
PCT: Procalcitonin
VAP: Ventilator-associated pneumonia
